# STUDY TO UNDERSTAND THE GENETICS of the acute response

# to metformin AND GLIPIZIDE in humans (*SUGAR MGH*)

# Background and Significance

***I.1. Genetic associations with type 2 diabetes***

**The risk of type 2 diabetes is strongly influenced by inheritance (**[**1**](#_ENREF_1)**).** In contrast with type 1 diabetes, where a single locus (the *HLA* region) explains a large proportion of the observed heritability, the genetic architecture of type 2 diabetes appears to be comprised of several variants, each of which has a modest impact on disease risk ([2](#_ENREF_2)). Despite significant advances in our understanding of the genetic determinants of the monogenic forms of diabetes ([3](#_ENREF_3)), the definitive identification of genes that increase risk of common type 2 diabetes in the general population has been far more laborious.

**One such diabetes-associated gene is *PPARG*¸ which encodes the peroxisome proliferator-activated receptor γ (PPARγ), a target for thiazolidinedione medications.** A proline → alanine change in codon 12 of *PPARG*  (P12A) has been consistently associated with type 2 diabetes ([4-10](#_ENREF_4)), with the proline allele conferring a ~20% increased risk under a recessive model. Because of its high frequency in the population, the population attributable risk of this variant nears 25% ([5](#_ENREF_5)). How this molecular change impairs protein function and leads to an increased risk of type 2 diabetes has not been fully elucidated; similarly, no discernible effects of this variant on diabetes-related traits have been consistently documented.

**A second gene is *KCNJ11*, which encodes the islet ATP-sensitive potassium channel Kir6.2.** Severe activating mutations in *KCNJ11* cause a novel form of monogenic neonatal diabetes ([11](#_ENREF_11)). A common glutamate → lysine change at position 23 (E23K) has also been consistently associated with type 2 diabetes with an overall allelic odds ratio of 1.15 ([12-18](#_ENREF_12)); normoglycemic lysine carriers seem to have a defect in insulin secretion ([15](#_ENREF_15); [18](#_ENREF_18); [19](#_ENREF_19)). In vitro, the risk lysine allele seems to affect potassium channel properties ([20](#_ENREF_20); [21](#_ENREF_21)).

**Recently, a comparable level of robust statistical significance has been achieved for the association of common variants in the transcription factor 7-like 2 gene (*TCF7L2*) with type 2 diabetes (**[**22**](#_ENREF_22)**).** These deCODE investigators documented that a common microsatellite (DG10S478) was associated with type 2 diabetes in an Icelandic case/control sample (N=2,116), and replicated this result in two additional case/control Caucasian cohorts (N=1,658). The overall estimated allelic relative risk was 1.56, with a P value of 7.8 x 10^-15^ (after Bonferroni correction for the number of alleles tested). The non-coding single nucleotide polymorphisms (SNPs) rs12255372 and rs7903146 were in strong linkage disequilibrium with DG10S478 (r^2^=0.95 and 0.78, respectively), and showed comparably robust associations with type 2 diabetes.

**The evidence accumulated for the above variants is convincing and well established.** While the field of genetic association studies is plagued by instances of irreproducibility ([23-26](#_ENREF_23)), many publications that have examined *PPARG* P12A and *KCNJ11* E23K have reported consistent results, such that the cumulative *P* value for these variants exceeds 10^-10^ ([27](#_ENREF_27)) and unpublished observations). The same level of evidence is being gathered for *TCF7L2*, where we and others have replicated this result in every population examined (see Section I.3 below).

**Since 2007 many more polymorphisms have been associated with type 2 diabetes and related traits.** The pace of discovery changed dramatically with the advent of genome-wide association studies (GWAS) ([28](#_ENREF_28)). The identification of millions of SNPs and their deposition in public databases; the manufacturing of genotyping arrays that could simultaneously query hundreds of thousands of SNPs with great precision; the understanding of an underlying correlation structure between SNPs, driven by the finite number of recombination events in human history, which reduced the complexity of the variation to be interrogated; the recognition that the scientific imperative of reproducibility required the acceptance of strict statistical thresholds that accounted for the universe of possible hypotheses in the human genome; and the corollary of such awareness, that for these very small *P* values to be achieved very large sample sizes had to be assembled through international collaboration, all coalesced to enable the pursuit of GWAS, where most of the common variants in the human genome (those with a minor allele frequency >5%) could be tested in one fell swoop. Several independent GWAS ([29-33](#_ENREF_29)) and the growing scientific exchange that led to successive meta-analyses of ever-increasing size ([34](#_ENREF_34); [35](#_ENREF_35)) soon produced a plethora of robust associations, such that the landscape of type 2 diabetes-associated variants grew from three prior to the GWAS era to several dozen in just a few years ([36](#_ENREF_36)). This list has been complemented by the implementation of similar approaches in the discovery of genetic determinants of quantitative glycemic traits ([37-42](#_ENREF_37)), the extension of GWAS to non-European populations ([43-48](#_ENREF_43)), and the deployment of custom-made arrays that allow for the rapid and efficient genotyping of top signals across thousands of additional samples ([49](#_ENREF_49); [50](#_ENREF_50)).

***I.2. Heterogeneity in pharmacological response***

**Not much is known about the basis of variable response to therapy in type 2 diabetes.** The long-recognized heterogeneity in patient response to treatment has not been studied systematically, such that in clinical practice diabetologists often choose first-line agents based on their side effect profile or known contraindications. Thus, although good reasons to select a particular agent exist (e.g. metformin to induce weight loss, a thiazolidinedione where insulin resistance is suspected), therapeutic decisions are made on a population basis, rather than being informed by more detailed knowledge of the particular characteristics of type 2 diabetes in each patient.

**As an example, preliminary evidence suggests the existence of a group of non-responders to thiazolidinedione medications.** Suter *et al.* studied the effects of troglitazone 400 mg daily in 11 subjects with type 2 diabetes, and found that 3/11 did not lower their fasting plasma glucose after a 6-12-week period of treatment; the change in fasting plasma glucose appeared to predict performance in an OGTT, a meal tolerance test and both glucose disposal and hepatic glucose production during a glucose-clamp study ([51](#_ENREF_51)). In a different study, 1/7 patients with IGT failed to show improvement in glucose tolerance after 12 weeks of troglitazone treatment (400 mg daily), 2/12 did not increase their glucose disposal rates after treatment, and 2/12 did not increase their insulin sensitivity index after treatment ([52](#_ENREF_52)). Similarly, 9/63 patients on 2 mg of rosiglitazone daily and 5/83 patients on 4 mg of rosiglitazone daily for 26 weeks had an increase in their HbA_1c_ at the end of the treatment period, rather than the expected decrease ([53](#_ENREF_53)). Finally, among Hispanic women with a history of gestational diabetes enrolled in the In the Troglitazone In the Prevention Of Diabetes (TRIPOD) study, 30% of women treated with troglitazone gained no protection from type 2 diabetes when compared with the placebo group, an effect attributed to their lack of improvement in insulin sensitivity ([54](#_ENREF_54)).

**Variability to drug response may have a genetic component.** For example, glyburide is metabolized by cytochrome P450 (*CYP2C9*), which has been found to contain two nonsynonymous polymorphisms (R144C and I359L) which affect its enzymatic activity and alter the clearance of glyburide ([55](#_ENREF_55)), ([56](#_ENREF_56)). Recently, Wolford *et al.* have shown that genetic variants in *PPARG* (other than P12A) may underlie the differential response to troglitazone shown in the TRIPOD participants ([57](#_ENREF_57)). Similarly, Sesti and colleagues recently reported a higher proportion of lysine carriers among subjects who failed sulfonylurea-metformin combined therapy (defined as a rise in fasting plasma glucose above 300 mg/dl); interestingly, islets isolated from lysine carriers showed a diminished insulin response to glibenclamide ([58](#_ENREF_58)).

**Despite the convincing associations of several genetic variants with type 2 diabetes and their involvement in physiological pathways involved in drug response, their impact on pharmacological interventions has not been systematically examined.** The completion of the Human Genome Project ([59](#_ENREF_59); [60](#_ENREF_60)) and the high-density characterization of common human variation in four different ethnic groups ([61](#_ENREF_61)) highlight the promise of genomic medicine. The elucidation of the genetic architecture of complex phenotypes may help clinicians understand disease heterogeneity, uncover new pathophysiological mechanisms, open the opportunity for novel therapeutic interventions, provide predictive diagnostic and prognostic information, and allow for individually tailored therapy that takes into account both the probability of response and the incidence of drug-induced complications ([62](#_ENREF_62)). *Our line of work, as elaborated in published reports, ongoing studies (see preliminary data below) and planned projects such as the Research Plan that follows, aims to contribute in the filling of this crucial translational gap.*

**Data from basic science and epidemiological studies support a link between glucose metabolism and the dietary intake of nutritents such as zinc, vitamin D, and calcium.** With regards to zinc intake, one might assume that impaired zinc transport in the β cell conferred by genetic variation may be attenuated by dietary zinc or zinc supplementation. Five genome-wide association scans for type 2 diabetes have confirmed a known type 2 diabetes loci at a missense single nucleotide polymporphism, rs13266634, in the gene SLC30A8 which encodes a β-cell zinc transporter ZnT-8 ([29-33](#_ENREF_29)). Prior studies have shown improvement in insulin sensitivity with zinc supplementation and epidemiologic studies have shown an association between higher dietary zinc and diabetes prevalence ([63](#_ENREF_63); [64](#_ENREF_64)). Given that zinc transport is essential for insulin secretion from the β cell, it could be hypothesized that high dietary zinc may not only lessen the risk of type 2 diabetes, but furthermore, accentuate the effect of sulfonureas on insulin secretion in the presence of certain risk SNPs, such as rs13266634. From the perspective of calcium and vitamin, the vitamin D receptor is expressed in β cells and the human insulin receptor gene has a vitamin D response element ([65](#_ENREF_65)). An NHANES study showed an inverse association between higher vitamin D status and type 2 diabetes in non-Hispanic whites and Mexican Americans ([66](#_ENREF_66)). The Nurses Health Study demonstrated lower risk of t2DM in individuals with higher calcium and vitamin D intake ([67](#_ENREF_67)). In order to further support vitamin D’s role in glucose metabolism, a recent study established that vitamin D and calcium supplementation improved fasting glucose and insulin resistance in subjects with impaired fasting glucose ([68](#_ENREF_68)). There has been conflicting data regarding the influence of Vitamin-D genetic variants on glycemic traits and type 2 diabetes incidence. Some studies have illustrated that Vitamin-D genetic variants are associated with insulin resistance. Given this interesting data, one might imagine that dietary vitamin D and vitamin D-associated genetic variants may not only influence insulin resistance, but possibly potentiate the glucose lower effects of metformin. *By obtaining dietary data from study participants,* o*ur proposed study hopes to elucidate the link between these dietary nutrients and associated genetic variants with glycemic traits and response to anti-diabetic medications.*

# *I.3. Preliminary Data*

**I.3.a. Studies on candidate genes that encode drug targets in type 2 diabetes**

**We have conducted well-powered, comprehensive genetic association studies designed to establish whether common variation in genes that encode drug targets are associated with type 2 diabetes.** By combining a well-phenotyped, large patient collection with a comprehensive approach to capture all common genetic variation in a given genomic region, we have been able to systematically pursue comprehensive association studies in candidate genes of high interest. Thus, we have completed the entire common haplotype structure of the genes encoding the sulfonylurea receptor (*ABCC8*) and its associated potassium channel (*KCNJ11*) ([18](#_ENREF_18)), the protein tyrosine phosphatase 1B (*PTPN1*) ([69](#_ENREF_69)), the insulin degrading enzyme (*IDE*) ([70](#_ENREF_70)), the seven AMP kinase genes ([71](#_ENREF_71)) and *TCF7L2* ([72](#_ENREF_72)). We have confirmed the published associations of the E23K variant of *KCNJ11* and rs7903146 in *TCF7L2* with type 2 diabetes ([18](#_ENREF_18); [72](#_ENREF_72); [73](#_ENREF_73)), and demonstrated that the K allele at *KCNJ11* E23K leads to decreased insulin secretion in normoglycemic subjects (Fig. 1).

Fig. 1: Differences in insulin secretion (as measured by the insulinogenic index) in normoglycemic individuals, depending on genotype at *KCNJ11* E23K (*P*<0.02).

**In addition to the comprehensive evaluation of common variation in candidate genes, we have tested specific genetic variants examined by other groups.** Through our long-standing collaborations with Drs. [name], [name] and [name], we have gained access to large patient collections that comprise both case/control and family-based samples. These samples have adequate power to reproduce previously published associations under specific genetic models, and their family-based components are robust to population stratification. While these samples have confirmed results widely observed by other groups, such as *PPARG* P12A ([5](#_ENREF_5)), *KCNJ11* E23K ([18](#_ENREF_18); [73](#_ENREF_73)) and *TCF7L2* (([72](#_ENREF_72)), we have been unable to replicate published associations in the genes that encode the insulin receptor substrate 1 (*IRS1*) ([73](#_ENREF_73)) and the ectoenzyme nucleotide pyrophosphate phosphodiesterase 1 *(ENPP1*) ([74](#_ENREF_74)), as well as *PTPN1* ([69](#_ENREF_69)) and *IDE* ([70](#_ENREF_70)).

**I.3.b. Prospective evaluation of associated polymorphisms**

[figure not shown]

P < 0.01

**We have examined these validated associations prospectively**. As part of the second Specific Aim in the PI’s K23 Research Career Development Award, and under the mentorship of [name], we have collaborated with the Diabetes Prevention Program (DPP) in testing whether specific genetic variants predict the development of diabetes in a multi-ethnic population of subjects with IGT and affect their response to preventive interventions. Consistent with prior cross-sectional studies, homozygotes for the proline allele in *PPARG* P12A progressed more rapidly from IGT to diabetes than alanine carriers (HR 1.24, 95% CI 0.99-1.57, *P*=0.07), with no interaction between genotype and intervention. There was a significant interaction of genotype x BMI, with a stronger relationship between BMI and progression to diabetes in alanine carriers. We detected no statistically significant effect of genotype on quantitative glycemic traits at baseline, nor on troglitazone response at one year (Florez *et al.,* in preparation).

Fig. 2: Effects of *KCNJ11* E23K genotype on baseline insulin to glucose ratio (IGR) in the Diabetes Prevention Program.

**The effect of *KCNJ11* E23K on development of diabetes and on related traits was more complex.** As previously reported in normal subjects, lysine carriers at *KCNJ11* E23K had reduced insulin secretion at baseline (Fig. 2). Nevertheless, EK heterozygotes were *less* likely to develop diabetes than EE homozygotes (HR 0.70, 95% CI 0.54-0.91, *P*<0.01), in a direction consistent with a large prospective study ([19](#_ENREF_19)). There was a novel interaction of metformin with E23K genotype (*P*=0.02): lysine carriers displayed a diminished preventive effect of metformin (HR 0.89 [95% CI 0.66-1.19] for EK and 0.95 [95% CI 0.54-1.67] for KK vs placebo), while EE homozygotes had a greater preventive effect (HR 0.55 [95% CI 0.42-0.71]).

**We have also replicated the association of *TCF7L2* with type 2 diabetes.** Over an average of 3 years, DPP participants with the risk TT genotype at rs7903146 were more likely to progress from IGT to diabetes than GG homozygotes (HR 1.55, 95% CI 1.20-2.01, *P*<0.001). The effect of genotype was stronger in the placebo group (HR 1.81, 95% CI 1.21-2.70, *P*<0.01) than in the metformin and lifestyle intervention groups (HR 1.62 and 1.15, respectively), although the genotype x intervention interaction was not statistically significant. Genotype was not associated with the response of these measures to intervention at one year. Similar results were obtained for rs12255372 ([75](#_ENREF_75)).

**I.3.c. Effects on quantitative glycemic traits**

**As mentioned above, *KCNJ11* E23K affects insulin secretion in normoglycemic individuals and in persons with IGT.** We ([18](#_ENREF_18)) and others ([15](#_ENREF_15); [19](#_ENREF_19)) have shown that the K allele leads to diminished insulin secretion during the initial phase of an OGTT in normoglycemic Caucasian individuals (Fig. 1); this effect is also seen in the multi-ethnic DPP cohort of individuals with IGT (Fig. 2) ([76](#_ENREF_76)).

**The lack of a preventive response to metformin noted in DPP participants with the KK genotype at *KCNJ11* E23K is correlated with a lack of improvement in insulin sensitivity.** While metformin seems to protect EE homozygotes at *KCNJ11* E23K, it does not delay or prevent the onset of diabetes in K allele carriers (see above). This lack of response may be explained by the obliteration of any improvement in insulin sensitivity observed in KK homozygotes, in contrast to the improvements noted in the lifestyle intervention and troglitazone arms (Fig. 3).

[figure not shown]

[figure not shown]

[figure not shown]

**Variants in *TCF7L2* also impair insulin secretion.** We have demonstrated lower insulinogenic index values both in normoglycemic ([72](#_ENREF_72)) and IGT ([75](#_ENREF_75)) individuals who carry the risk TT genotype at *TCF7L2* rs7901346 when compared to CC homozygotes (in control individuals, the insulinogenic index was 0.61 ± 0.71 vs 1.00 ± 1.84, *P* <0.001; mean ± SD). This transcription factor is postulated to influence expression of GLP-1 ([22](#_ENREF_22)), an enteroendocrine incretin which activates insulin secretion after a meal ([77](#_ENREF_77)). Thus, while a glucose oral load might be expected to elicit different insulin secretory responses depending on variation at *TCF7L2*, bypassing GLP-1 by intervening at a more distal step in the insulin secretion pathway should eliminate the immediate genetic consequences of *TCF7L2* variants. Whether GLP-1 levels are actually different according to *TCF7L2* genotype has not been measured directly.

Fig. 3: Insulin sensitivity Index (ISI) according to *KCNJ11* E23K genotype one year after a lifestyle intervention, metformin or troglitazone. ISI does not improve in KK homozygotes after metformin treatment (*P*<0.01).

**This proposal intends to validate and extend these observations.** While *KCNJ11* E23K is known to impair insulin secretion, whether allelic variation at this locus affects the acute response to sulfonylurea treatment in vivo has not been determined. In addition, the proposed mechanism of action of *TCF7L2* in regulating insulin secretion via GLP-1 (or glucagon) has not been tested. Finally, it is not clear whether the unexpected lack of improvement in insulin sensitivity in individuals with the KK genotype at *KCNJ11* after metformin treatment is an acute or chronic effect, or merely a statistical fluctuation. *The pilot studies proposed here intend to answer these questions and set the stage for an outcomes-based clinical trial that extends these pharmacogenetic findings into the clinical arena.*

# Statement of Hypothesis and Specific Aims

**Given these preliminary findings, we hypothesize that variants in genes that are reproducibly associated with type 2 diabetes or related traits may impact the effect of anti-diabetic medications.** In particular, sulfonylureas may have differential effects on individuals depending on the allelic variant they carry at *KCNJ11* E23K; conversely, because *TCF7L2* is postulated to influence insulin secretion by regulating levels of glucagon-like peptide 1 (GLP-1), and sulfonylureas act at a more distal step in the insulin secretion pathway, the effect of sulfonylureas on insulin secretion should be independent of genetic variation at *TCF7L2*. Finally, it is not known whether the effect of metformin on insulin sensitivity in KK homozygotes at *KCNJ11* occurs in the acute setting or only after long-term treatment.

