**We therefore propose the following Specific Aims:**

Specific Aim No.1: To examine the acute response to a sulfonylurea challenge (glipizide 5 mg orally) in subjects at risk of diabetes or with early diabetes (on diet treatment alone), depending on genotype at *KCNJ11* E23K, *TCF7L2* rs7903146, or newly discovered variants linked to type 2 diabetes via associations with related phenotypes, individually or in aggregate

- We hypothesize that subjects with a subset of variants will have an attenuated response, whereas those with a different subset will have no discernible impact on this response

Specific Aim No. 2: To examine the acute response to short-term metformin treatment on the insulin sensitivity index in the same group, depending on genotype at *KCNJ11* E23K, or newly discovered variants linked to type 2 diabetes via associations with related phenotypes, individually or in aggregate

- We hypothesize that subjects with a subset of variants will have a diminished improvement in insulin sensitivity compared to non-carriers

Specific Aim No. 3: To examine acute insulin secretion (by the insulinogenic index derived from an OGTT), GLP-1 and glucacon levels, and metabolomic profiling after short-term metformin treatment (500 mg bid x 4 doses) in the same group of subjects, depending on genotype at *TCF7L2* rs7903146, or newly discovered variants linked to type 2 diabetes via associations with related phenotypes, individually or in aggregate

- We hypothesize that subjects with the risk TT genotype at *TCF7L2* rs7903146, or a subset of variants will have a reduced insulinogenic index and GLP-1 levels than non-carriers

***If successful, this proposal should help clarify the pathophysiologic mechanisms by which these key genetic variants increase risk of type 2 diabetes, and assess their impact on commonly used antidiabetic treatments. In addition, this pilot study will lay the groundwork for a long-term, outcomes-based pharmacogenetic clinical trial.***

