***VI.1. Study endpoints***

**The study will have the following primary endpoints, according to each Specific Aim:**

Specific Aim No. 1 – Sulfonylurea challenge: Trough glucose and peak insulin levels will be compared by genotype. Secondary endpoints will be differences in glucose and insulin areas under the curve (AUC, calculated by the trapezoidal method), as well as glucose and insulin at 2 hours. Leftover serum samples will be frozen for glucagon level measurements.

Specific Aim No. 2 – Acute metformin effect on insulin sensitivity: The insulin sensitivity index (reciprocal of insulin resistance by homeostasis model assessment ([84](#_ENREF_84))) will be calculated as 22.5/[fasting insulin x (fasting glucose/18.01)], and compared by genotype. A secondary endpoint will be differences in the insulinogenic index by genotype after metformin treatment, calculated as [(insulin at 30 min) – (insulin at 0 min)]/[(glucose at 30 min) – (glucose at 0 min)].

Specific Aim No. 3 – insulinogenic index and GLP-1 levels during OGTT: The insulinogenic index, calculated as above, will be compared by genotype, and the differences between genotypic groups will be contrasted to those observed during the sulfonylurea challenge (Specific Aim No. 1). A subset of subjects (selected to have equal numbers in each genotypic group) will have their GLP-1 levels measured, and peak GLP-1 as well as AUC will be compared by genotype. Leftover serum samples will be frozen for metabolomic profiling and glucagon level measurements.

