***VI.2. Statistical analysis***

**Non-normal variables will be log transformed.** They will be adjusted for age, gender and BMI, and residuals will be compared between each group of homozygous individuals at each locus by Student t tests. Since these polymorphisms may influence glycemic traits by affecting BMI, both BMI-adjusted and unadjusted analyses will be reported. Secondary analyses will include exploration of genetic models (dominant, recessive or additive), by including heterozygous individuals and performing ANOVA across the three genotypic groups, with subsequent Bonferroni adjustment for multiple comparisons. The role of self-reported ethnicity will be evaluated with an interaction term; analyses will also be repeated within each self-reported ethnic group, and in the aggregate of groups where minor allele frequencies are comparable. As these experiments involve validation of previous hypotheses, nominal *P* values below 0.05 will be considered statistically significant.

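### Independence of glipizide response from TCF7L2 is predicted but only difference tests are planned, and the OGTT-versus-glipizide contrast has no common scale and no test

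*Protocol*

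**What the plan says.** The Statement of Hypothesis predicts that "the effect of sulfonylureas on insulin secretion should be independent of genetic variation at *TCF7L2". Section I.3.c gives the reason: TCF7L2 is thought to act through GLP-1, and a sulfonylurea acts further down the secretory pathway. Specific Aim 1 carries a prediction of the same type, without naming the locus: some variants attenuate the response, "whereas those with a different subset will have no discernible impact on this response".

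Section VI.1 sets the measures. For the glipizide challenge, "Trough glucose and peak insulin levels will be compared by genotype"; glucose and insulin AUC and 2-hour values are secondary. For Aim 3 the measure is the insulinogenic index from the OGTT, a ratio of the 0-to-30-minute changes in insulin and glucose. Within that primary endpoint, "the differences between genotypic groups will be contrasted to those observed during the sulfonylurea challenge".

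Section VI.2 sets the analysis: "residuals will be compared between each group of homozygous individuals at each locus by Student t tests", with ANOVA across three genotypes as secondary and nominal P below 0.05 as the threshold. Its only interaction term is for ethnicity. Section VI.3 gives power for detecting differences only.

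**The concern.** A test of difference can reject equality but cannot confirm it. Where the predicted result is no effect, low precision makes the predicted result more likely to appear. The protocol gives no margin and no confidence-interval rule that would separate a small effect from an imprecise estimate.

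The contrast has a second problem. If the TT-versus-CC difference is significant in the OGTT and not after glipizide, that does not show that the two differences differ. It cannot be shown on the listed primary measures either, because a ratio index and a peak or trough level share no scale. The index does not carry over to the glipizide challenge: glucose is expected to fall there (VII.1), so the denominator would be negative or near zero.

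At stake is the mechanistic conclusion that TCF7L2 acts upstream of the step glipizide stimulates. The KCNJ11 comparisons are not affected.

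**Working it through.** **Inputs from the protocol.** N = 750, T allele frequency 0.32, K allele frequency 0.35, Hardy-Weinberg proportions, and 94% power for a 20% peak-insulin difference at one-sided 0.05 (all VI.3). Insulinogenic index 0.61 (SD 0.71) in TT and 1.00 (SD 1.84) in CC (I.3.c).

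**Group sizes.** TT = 750 × 0.32² = 76.8; CC = 750 × 0.68² = 346.8. For KCNJ11, KK = 750 × 0.35² = 91.9 and EE = 750 × 0.65² = 316.9.

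**The plan's own figures.**
- Insulinogenic index, stated as above 80% one-sided. With separate variances, SE = √(0.71²/76.8 + 1.84²/346.8) = 0.128, and power = Φ(0.39/0.128 − 1.645) = 92%. The statement is reproduced on that basis.
- Peak insulin, stated as 94%. This cannot be reproduced because no SD is given, so it is inverted.

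**Implied standard error.** SE = 20/(1.555 + 1.645) = 6.25 points if the 94% refers to TT versus CC. If it refers to KCNJ11, the TT-versus-CC value is 6.25 × √[(1/77 + 1/347)/(1/92 + 1/317)] = 6.65.

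**Chance that a true 10% peak-insulin difference is non-significant.** VI.2 does not state sidedness, so both are shown.
- Two-sided: Φ(1.96 − 10/6.25) = 64%; with SE 6.65, 68%.
- One-sided: Φ(1.645 − 10/6.25) = 52%; with SE 6.65, 56%.
- At N = 1,000 the more favourable SE becomes 6.25 × √0.75 = 5.41, giving about 54% and 42%.

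**Equivalence power.** With a true difference of zero and the 90% confidence-interval rule, power = 2Φ(margin/SE − 1.645) − 1. The margins are assumptions.

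| Margin | N = 750, SE 6.25 | N = 750, SE 6.65 | N = 1,000, SE 5.41 |
| --- | --- | --- | --- |
| 20% | 88% | 83% | 96% |
| 15% | 55% | 46% | 74% |
| 10% | 0% | 0% | 16% |

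**Is 20% a usable margin?** With a true 10% difference and a 20% margin, independence would be declared with probability about Φ((20 − 10)/6.25 − 1.645) = 48%, or 44% with SE 6.65. The detectable difference in VI.3 is therefore not a justified margin merely because the study is powered for it.

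**Formal contrast, illustrative.** Take the OGTT effect as 0.39/1.69 = 0.23 pooled SDs (1.69 being the pooled SD), a zero glipizide effect, both visits observed in all subjects, and an assumed within-subject correlation ρ of 0 to 0.7. SE = √[2(1 − ρ)] × √(1/76.8 + 1/346.8), which is 0.178 at ρ = 0 and 0.098 at ρ = 0.7. Two-sided power is Φ(0.23/0.178 − 1.96) = 25%, rising to 65% at ρ = 0.7.

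**The case against.** The strongest reply is that the misuse is not written down. A reader might infer that the protocol will treat a non-significant t test as proof of independence. No section says so: the hypothesis is a mechanistic expectation, and VI.2 states only when a result is significant. A reader might also take half of Aim 1 to be a no-effect hypothesis. The aim covers KCNJ11, TCF7L2 and newly discovered variants, and its no-impact clause does not name TCF7L2. Nor is it right that the study could never support independence: the planned data can exclude differences near 20%, and a reported confidence interval would show that. These points stand, and they limit the criticism to what the plan lacks.

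A second reply is that margins and model details are commonly left to a statistical analysis plan, and that the protocol calls the study a pilot. This stands only in part. VI.2 itself fixes the test and the significance rule, and VI.1 puts the contrast inside a primary endpoint. The objection is that what is fixed does not match what is hypothesised.

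A third reply is that Aim 1 also lists AUC and 2-hour values, and that both visits sample insulin at 0, 30, 60 and 120 minutes. That is correct, and it is why a repair is possible. But VI.1 lists no insulin AUC for the OGTT and links no common measure to the contrast.

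Finally, a genotype-by-challenge test would not isolate the mechanism. The OGTT is done on metformin (V.5) and the glipizide challenge comes before metformin (V.2), so stimulus and metformin exposure are mixed. This stands and limits what the repair can claim.

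**Conclusion.** The point holds, as something that should be corrected. The plan contains no analysis that could support its prediction of independence, and its OGTT-versus-glipizide contrast is an informal comparison of different measures under different drug conditions. At N = 750, a real 10% peak-insulin difference would be missed 64–68% of the time two-sided, or 52–56% one-sided.

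These figures rest on a standard error back-calculated from the 94% statement, with neither the SD nor the locus given, and on a normal approximation. The equivalence figures also rest on assumed margins, and the contrast figures on assumed correlations. A reader might infer that the present sample is adequate for an equivalence claim. That is so only near a 20% margin, which the protocol does not justify for this use.

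**What to change.** In VI.1 and VI.2:

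- Report the TT-versus-CC difference in glipizide response with its confidence interval, and state that non-significance alone is not evidence of independence. Conclude independence only if the 90% confidence interval lies inside a margin that the sponsor justifies in advance. Otherwise report the result as inconclusive.
- Replace the informal contrast with a within-subject genotype-by-challenge test on one measure available at both visits: baseline-adjusted log insulin AUC over 0–120 minutes, from the shared 0, 30, 60 and 120 minute samples. The AUC is preferable to insulin at 30 minutes, because V.6 puts the initial glipizide response at about that time. Label the test exploratory, because metformin differs between the challenges and power is modest.

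The cost is a paragraph in the protocol and one extra model on data already planned. The sponsor has to defend a margin, a tight margin may leave the result inconclusive at this sample size, and a null t test can no longer be offered as support.
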